## STATEMENT OF COMPLIANCE

The trial will be conducted in accordance with the ethical principles that have their origin in the Declaration of Helsinki, and that are consistent with GCP and the applicable regulatory requirement(s).

The rights, safety and well-being of the trial subjects are the most important considerations and should prevail over interests of science and society.

A trial will be conducted in compliance with the protocol that has received prior institutional review board (IRB)/independent ethics committee (IEC) approval/favorable opinion.

Every individual involved in conducting a trial should be qualified by education, training, and experience to perform his or her respective task(s). Freely given informed consent will be obtained from every subject prior to clinical trial participation.

All clinical trials information will be recorded, handled, and stored in a way that allows its accurate reporting, interpretation and verification.

The confidentiality of records that could identify subjects will be protected, respecting the privacy and confidentiality rules in accordance with the applicable regulatory requirements(s).

Test products will be manufactured, handled, and stored in accordance with applicable good manufacturing practice (GMP). They will be used in accordance with approved protocol.

|                                                                                  |                                                                                                       |                                                              |
|----------------------------------------------------------------------------------|-------------------------------------------------------------------------------------------------------|--------------------------------------------------------------|
| [figure not shown] | Clinical trial to evaluate efficacy and safety of Amla Extract (AMX160) in patients with Dyslipidemia | Project No. AN-03ASE
0115H2-SYN02
Ver.01, Dt: 01-01-15 |
|----------------------------------------------------------------------------------|-------------------------------------------------------------------------------------------------------|--------------------------------------------------------------|

## Abbreviations

| Sr. No. | Abbreviation | Full Form                             |
|---------|--------------|---------------------------------------|
| 1.      | AE           | Adverse Event                         |
| 2.      | AIP          | Atherogenic Index of Plasma           |
| 3.      | ApoA1        | Apo lipoprotein A1                    |
| 4.      | ApoB         | Apo lipoprotein B                     |
| 5.      | CAD          | Coronary Artery Disease               |
| 6.      | CHD          | Coronary Heart Disease                |
| 7.      | CRA          | Clinical Research Associate           |
| 8.      | CRF          | Case Record Form                      |
| 9.      | EC           | Ethics Committee                      |
| 10.     | FBS          | Fasting Blood Sugar                   |
| 11.     | GCP          | Good Clinical Practise                |
| 12.     | HbA1c        | Glycosylated Haemoglobin              |
| 13.     | HDL          | High Density Lipoproteins             |
| 14.     | HMG Co-A     | 3-hydroxy-3-methylglutaryl-coenzyme A |
| 15.     | ICF          | Informed Consent Form                 |
| 16.     | IEC          | Institutional Ethics Committee        |
| 17.     | IRB          | Institutional Review Board            |
| 18.     | LAR          | Legally Acceptable Representative     |
| 19.     | LDL          | Low Density Lipoproteins              |
| 20.     | mg           | Milligram                             |
| 21.     | mITT         | Modified Intention to Treat           |
| 22.     | PP           | Per Protocol                          |
| 23.     | QA           | Quality Assurance                     |
| 24.     | SAE          | Serious Adverse Event                 |
| 25.     | SD / SE      | Standard Deviation / Standard Error   |
| 26.     | TC           | Total Cholesterol                     |
| 27.     | TG           | Triglycerides                         |
| 28.     | PIS          | Patient Information Sheet             |
| 29.     | Urine R/M    | Urine Routine and Micro test          |
| 30.     | VLDL         | Very Low Density Lipoproteins         |

[figure not shown]

| [figure not shown] | Clinical trial to evaluate efficacy and safety of Amla Extract (AMX160) in patients with Dyslipidemia | Project No. AN-03ASE
0115H2-SYN02
Ver.01, Dt: 01-01-15 |
|----------------------------------------------------------------------------------|-------------------------------------------------------------------------------------------------------|--------------------------------------------------------------|

## 1 Background and Introduction

Dyslipidaemia is one of the most frequently implicated risk factors for development of atherosclerosis. A strong association exists between hyperlipidaemia and coronary artery disease (CAD), cerebrovascular stroke, and peripheral vascular disease. In the peripheral circulation, it can cause intermittent claudication and gangrene and can jeopardize limb viability. The hypolipidaemic medications have attracted considerable attention because of their potential to prevent cardiovascular disease by retarding the accelerated atherosclerosis in hyperlipidaemic individuals. The medications used in the management of hyperlipidaemia are bile acid sequestrants, nicotinic acid, fibric acid derivatives, and 3 - hydroxy - 3 - methylglutaryl - coenzyme A (HMG Co - A) reductase inhibitors. Although all these medications are effective in the management of dyslipidaemia, they are associated with significant side effects like hepatitis, rhabdomyolysis, myopathy, etc. and thus search for safer alternatives continues.

Various medicinal plants used in the traditional systems of medicine have shown immense potential in management of dyslipidaemia and CAD without major adverse events. *Emblica officinalis* (Amla or Indian gooseberry) is one such medicinal plant which has been shown to be effective in management of dyslipidaemia in experimental animals and in pilot clinical studies without major side effects.

In vitro and animal studies have shown that the flavonoids from *E. officinalis* effectively reduce lipid levels in serum and tissues and exert a significant inhibitory effect of hepatic HMG CoA reductase enzyme activity. Previous studies in rabbits have confirmed that Amla Extract of M/s Arjuna Natural Extracts Limited in effective management of dyslipidaemia by reducing Low Density Lipoproteins (LDL) and increasing the High Density Lipoproteins (HDL) levels. Beside the effect on serum lipids, Amla Extract is also known to have potent anti-oxidant effects as established in several test systems such as superoxide radicals, lipid peroxide formation induction by Fe+++ /ADP ascorbate system, hydroxyl radical scavenging action and in systemic augmentation of antioxidant enzymes in the brain of laboratory animals.

A few pilot clinical studies have also shown the beneficial effects of Amla Extract in patients with dyslipidaemia. In a non-comparative clinical study, Amla Extract of M/s Arjuna Natural Extract Limited at doses of 500 mg/day and 1000 mg/day significantly reduced the levels of risk factors of CAD arising from dyslipidaemia and inflammation. In another placebo controlled trial, Amla Extract of M/s Arjuna Natural Extract Limited at a dose of 500 mg twice daily, showed a significant reduction in Total Cholesterol (TC), LDL, Very Low Density Lipoproteins (VLDL) and Triglycerides (TG) and a significant increase in serum HDL as compared to placebo over a period of 4 months. Another clinical study comparing the efficacy and safety of Amla Extract (500 mg/day) with Simvastatin (20 mg/day) has not shown any difference in the beneficial effects of the two active treatments on TC, LDL and HDL.

|                                                                                  |                                                                                                       |                                                              |
|----------------------------------------------------------------------------------|-------------------------------------------------------------------------------------------------------|--------------------------------------------------------------|
| [figure not shown] | Clinical trial to evaluate efficacy and safety of Amla Extract (AMX160) in patients with Dyslipidemia | Project No. AN-03ASE
0115H2-SYN02
Ver.01, Dt: 01-01-15 |
|----------------------------------------------------------------------------------|-------------------------------------------------------------------------------------------------------|--------------------------------------------------------------|

This clinical study is being planned to assess the efficacy and safety of Amla Extract of M/s Arjuna Natural Extracts Limited, Kerala for management of dyslipidaemia. Beside the conventional lipid parameters like TG, TC, LDL, and HDL various other parameters have shown correlation with progression of coronary artery disease. The most important of these parameters include the Atherogenic Index of Plasma (AIP), Apo lipoproteins A1, Apo lipoprotein B and their ratio, Homocysteine levels, Coenzyme Q10 and chronic inflammatory markers like hs-CRP. This study is being planned to assess the effect of Amla Extract of M/s Arjuna Natural Extracts Limited, Kerala on these parameters besides the effect on the conventional lipid parameters. Moreover, as Amla Extract is known to have an effect on blood sugar levels, HbA1c and fasting glucose shall also be measured during the study.

## 2 Study Rationale

Randomized, double blind, placebo controlled studies are considered to be of the highest standards for the assessment of efficacy and safety of a study medication; accordingly the same design is used for this study. Patients with dyslipidaemia will be enrolled in the study to assess the effect of Amla Extract (AMX160) on lipid levels. Patients with severe disease or having 2 or more risk factors as per the ATP III guidelines will not be enrolled in the study as this is a placebo controlled trial and half of the patients in the study will not be receiving any active treatment. As most of the lipid lowering agents provide a peak action by 4 weeks and also various international clinical studies evaluating the efficacy and safety of medications for dyslipidaemia have a 12 week study period, a follow up of 12 weeks is planned in the study. Moreover, long term study cannot be justified with a placebo arm. All the patients enrolled in the study will also be asked to initiate lifestyle changes (healthy diet with aerobic exercise at least 4 days a week) along with the study medication.

## 3 Study Objective

The objective of this clinical study is to evaluate the efficacy and safety of Amla Extract (AMX160) of M/s Arjuna Natural Extracts Limited, Kerala as compared to the matching placebo in patients with dyslipidaemia aged 30-65 years.

## 4 Study Design

### 4.1 Overview of the study design

#### 4.1.1 Type of study

A prospective, randomized, double blind, parallel, placebo controlled, multicentre, clinical study

|                                                                                  |                                                                                                       |                                                              |
|----------------------------------------------------------------------------------|-------------------------------------------------------------------------------------------------------|--------------------------------------------------------------|
| [figure not shown] | Clinical trial to evaluate efficacy and safety of Amla Extract (AMX160) in patients with Dyslipidemia | Project No. AN-03ASE
0115H2-SYN02
Ver.01, Dt: 01-01-15 |
|----------------------------------------------------------------------------------|-------------------------------------------------------------------------------------------------------|--------------------------------------------------------------|

#### **4.1.2 Study groups**

Test group: Amla Extract (AMX160) 500 mg capsule of M/s Arjuna Natural Extracts Limited, Kerala

Reference group: Matching Placebo

#### **4.1.3 Number of study subjects and subject number assignment**

A total of 98 patients at multiple centres in India will be simultaneously enrolled in this clinical trial to compare the efficacy and safety of the test versus reference product (refer section 14.1 for details of sample size calculation). The enrolled patients would be assigned to either of the 2 study groups according to the centralized computer generated randomization in a 1:1 ratio.

#### **4.1.4 Type, sequence and duration of study periods**

This is a parallel treatment group study and all the enrolled patients will be instructed to take study medication for a treatment period of 12 weeks. There will be a total of 5 visits: Screening, Randomization (Day 0), Follow up (Week 4), Follow up (Week 8) and End of study visit (Week 12). Laboratory investigation of all the efficacy parameter will be conducted at screening, on all follow up visits and end of study while laboratory investigations for safety will be carried out on screening and end of the study.

|                                                                                  |                                                                                                       |                                                              |
|----------------------------------------------------------------------------------|-------------------------------------------------------------------------------------------------------|--------------------------------------------------------------|
| [figure not shown] | Clinical trial to evaluate efficacy and safety of Amla Extract (AMX160) in patients with Dyslipidemia | Project No. AN-03ASE
0115H2-SYN02
Ver.01, Dt: 01-01-15 |
|----------------------------------------------------------------------------------|-------------------------------------------------------------------------------------------------------|--------------------------------------------------------------|

## 4.2 Flow chart of the study

[figure not shown]

## 4.3 Brief description of the methods and procedures

Patients with dyslipidaemia aged 30-65 years will be evaluated as per the Inclusion & Exclusion Criteria as mentioned below (section 6) and will undergo a thorough physical (general and systemic) examination and appropriate laboratory investigations (mentioned in section 7.3) to rule out other concomitant diseases during the screening visit. Eligible patients will receive either Amla Extract (AMX160) 500 mg capsule of M/s Arjuna Natural Extracts Limited, Kerala or a matching placebo capsule twice daily according to a centralized computer generated randomization plan. This would be a double blind study and hence, neither the investigator nor the patients will know which medication is being dispensed to him. All the patients enrolled in the study will also be asked to initiate lifestyle changes (healthy diet with exercise at least 4 days a week) along with the study medication.

|                                                                                  |                                                                                                       |                                                              |
|----------------------------------------------------------------------------------|-------------------------------------------------------------------------------------------------------|--------------------------------------------------------------|
| [figure not shown] | Clinical trial to evaluate efficacy and safety of Amla Extract (AMX160) in patients with Dyslipidemia | Project No. AN-03ASE
0115H2-SYN02
Ver.01, Dt: 01-01-15 |
|----------------------------------------------------------------------------------|-------------------------------------------------------------------------------------------------------|--------------------------------------------------------------|

After randomization, patients will be followed up on outpatient basis for period of 84 days (12 weeks) with scheduled visits on day 28, day 56 and day 84 post-randomization. Efficacy assessments will be carried out by laboratory investigations on each of the scheduled visits (except randomization visit). Clinical adverse events monitoring would be done on each visit and complete laboratory check-ups (both haematological and biochemical) and ECG will be repeated at the end of the study (12 weeks) so as to assess the safety of the study medication. Laboratory values obtained during the screening visit will be considered as baseline values for efficacy and safety analysis. Though every effort will be made to adhere to the schedule of visits, a window period of  $\pm 5$  days will be permitted for all the visits.

#### **4.4 Brief discussion of study design**

This will be a randomized, double blind, parallel, placebo controlled, multicentre study to evaluate the efficacy and safety of Amla Extract (AMX160) 500 mg capsule of M/s Arjuna Extract Limited, Kerala compared to a placebo capsule in patients with dyslipidaemia. Randomization prevents selection / treatment allocation bias and blinding will prevent the bias in the assessment of efficacy and safety (adverse events) due to the study medication. Randomized patients will be simultaneously enrolled in either study group as per their randomization number and will be followed up in a parallel manner till the completion of study.

### **5 Study Population**

Patients with dyslipidaemia aged 30-65 years will be enrolled in this study. A total of 98 patients at multiple centres will be simultaneously enrolled in this clinical study. Enrolment of patients at study sites would be competitive i.e. if enrolment is slow or inadequate at one site, then more number of patients may be enrolled at other sites in order to complete the study

### **6 Subject Eligibility**

#### **6.1 Inclusion Criteria**

- 1 Patients aged 30-65 years
- 2 Patients with dyslipidaemia having Triglycerides (TG) >200 mg/dL, LDL cholesterol > 130 mg/dL, Total cholesterol > 200 mg/dL and HDL cholesterol < 40 mg/dL for men and < 50mg/dL for women
- 3 Patients not taking any medication (including herbal product) for management of dyslipidaemia since last 4 weeks
- 4 Informed consent of the patient

|                                                                                  |                                                                                                       |                                                              |
|----------------------------------------------------------------------------------|-------------------------------------------------------------------------------------------------------|--------------------------------------------------------------|
| [figure not shown] | Clinical trial to evaluate efficacy and safety of Amla Extract (AMX160) in patients with Dyslipidemia | Project No. AN-03ASE
0115H2-SYN02
Ver.01, Dt: 01-01-15 |
|----------------------------------------------------------------------------------|-------------------------------------------------------------------------------------------------------|--------------------------------------------------------------|

## 6.2 Exclusion Criteria

1. Patients with more than 2 of the following risk factors -
  - Cigarette smoking
  - Hypertension (BP >140/90 mmHg or on antihypertensive medication)
  - Family history of premature CHD (CHD in male first degree relative <55 years; CHD in female first degree relative <65 years)
  - Age (men >45 years; women >55 years)
2. Patients with uncontrolled cardiovascular disease or advanced atherosclerosis (e.g. history of stroke, myocardial infarction, life-threatening arrhythmia, or coronary revascularization within the preceding 6 months; unstable angina; congestive heart failure; known or suspected clinically significant valvular heart disease or uncontrolled hypertension (>160/100 mm of Hg or use of antihypertensive medications, dose of which is not stable in the last one month))
3. Patients with very high triglyceride levels i.e. > 500 mg/dL
4. Patients with FBS more than 150 mg/dL, using insulin, glitazones. Patients using other hypoglycaemics, dose of which is not stable in last one month
5. Pregnancy, lactation and female patients not using acceptable contraceptive measures (double barrier methods, oral or injectable hormonal contraceptives or surgical sterilization)
6. Patients with hepatic impairment (SGOT or SGPT levels > 3 Upper Limit of Normal (ULN)) or renal impairment (serum creatinine  $\geq$  2.0 mg/dl)
7. Patients with any other severe systemic illness and in the opinion of the investigator would be noncompliant with the visit schedule or study procedures
8. Patients with known history of hypersensitivity to amla or any product containing amla extract
9. Patients with continuing history of alcohol and / or drug abuse.
10. Patients with any other serious concurrent illness or malignancy.
11. Participation in another clinical trial in the past 3 months

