## 8 Study Conduct

The patients fulfilling the inclusion and exclusion criteria will be enrolled in the trial and will be randomized to receive either of the study medications in a double blinded

|                                                                                  |                                                                                                       |                                                              |
|----------------------------------------------------------------------------------|-------------------------------------------------------------------------------------------------------|--------------------------------------------------------------|
| [figure not shown] | Clinical trial to evaluate efficacy and safety of Amla Extract (AMX160) in patients with Dyslipidemia | Project No. AN-03ASE
0115H2-SYN02
Ver.01, Dt: 01-01-15 |
|----------------------------------------------------------------------------------|-------------------------------------------------------------------------------------------------------|--------------------------------------------------------------|

manner. The patients will be followed on an outpatient basis as per the schedule of visits mentioned below. Though every effort will be made to adhere to the schedule of visits, a window period of  $\pm 5$  days for will be permitted. Further, on all the scheduled visits the following assessments will be done and recorded in the CRF.

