#### Visit 2: Randomization (Day 0)

- Inclusion & Exclusion Criteria re-check
- General physical and systemic examination
- Laboratory investigations - If patient satisfies all inclusion and exclusion criteria, other investigations i.e. Apo A1, Apo B, hs CRP, TSH, Homocysteine CoQ10, HbA1c and HMG Coenzyme Reductase activity will be done utilizing the same blood sample as collected at time of screening. No fresh blood sample will be collected on this visit
- Randomization and dispensing of study medication
- Recording of concomitant diseases and medications
- Instructions for lifestyle modification (healthy diet with aerobic exercise at least 4 days a week)

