### **8.1 Protocol violation, deviation, waiver or amendments**

During this study examples of deviations may include, but are not limited to:

- Participant seen outside window period ( $\pm$  5 days)
- Missed or incomplete study procedure (e.g. examination)

During this study following will be considered as protocol violations:

- Failure to report within  $\pm$  7 days
- Failure to obtain written informed consent
- Missing Informed Consent Form (ICF)
- ICF does not contain all the required signatures
- ICF used was not the current EC approved version
- Participant did not meet eligibility criterion
- Prescribed dosing outside protocol guidelines
- A breach of confidentiality
- Falsifying research or medical records
- Participant receives wrong treatment
- Randomization of participant prior to EC approval of protocol
- Subject withdrawal criteria not followed
- Use of prohibited concomitant treatments

Any deviation or violation from the Protocol should be duly explained with justification(s) thereof by the concerned investigator. The Investigator should promptly report to the Ethics Committee, sponsor's representative / medical expert, deviation / violation from the Protocol, if any which may cause immediate hazards to the subjects. There will be no protocol waiver in this study. Subjects dropped out before the study completion will not be replaced. Patients violating the Protocol will

|                                                                                  |                                                                                                       |                                                              |
|----------------------------------------------------------------------------------|-------------------------------------------------------------------------------------------------------|--------------------------------------------------------------|
| [figure not shown] | Clinical trial to evaluate efficacy and safety of Amla Extract (AMX160) in patients with Dyslipidemia | Project No. AN-03ASE
0115H2-SYN02
Ver.01, Dt: 01-01-15 |
|----------------------------------------------------------------------------------|-------------------------------------------------------------------------------------------------------|--------------------------------------------------------------|

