not be included in the Per Protocol efficacy analysis while all the patients (including those with deviations and violations) will be considered for modified Intention To Treat efficacy analysis if they have completed visit 3 (week 4) with laboratory evaluation. All the subjects who have been dispensed study medication and have completed visit 3 (week 4) will be considered for safety evaluation.

Neither the investigator nor Arjuna Natural Extracts Limited will alter this study protocol. Amendments should be made only in exceptional cases once the study has started. Any change in the protocol should be approved by IEC / IRB, wherever necessary before implementation.

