### 11.2 Risk / benefit assessment

This study includes interventions offering the prospect of direct health-related benefit to the patient. To establish with certainty that the therapeutic efficacy of Amla Extract (AMX160) in Indian patients is not due to placebo effect; placebo comparator is selected. Patients enrolled in the study will have risk of lack of efficacy of study medication but all the patients will be encouraged for life style modification during the study period.

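### Section 2 keeps patients with two or more risk factors out of this placebo-controlled trial, but exclusion criterion 1 keeps out only those with more than two

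*Protocol*

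**What the plan says.** Protocol section 2 (Study Rationale) states that patients with severe disease or "having 2 or more risk factors as per the ATP III guidelines will not be enrolled in the study", and gives the reason: "as this is a placebo controlled trial and half of the patients in the study will not be receiving any active treatment".

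Protocol section 6.2 (Exclusion Criteria), item 1, excludes "Patients with more than 2 of the following risk factors". Four factors follow: cigarette smoking; hypertension, defined by blood pressure or by treatment; a family history of premature coronary heart disease; and age (men above 45, women above 55).

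The criteria decide entry. Section 8 says: "The patients fulfilling the inclusion and exclusion criteria will be enrolled in the trial and will be randomized". The Visit 2 list in the same section includes "Inclusion & Exclusion Criteria re-check". Sections 4.3 and 7 likewise assess patients against the inclusion and exclusion criteria. Nothing sends a site to section 2 to decide on entry.

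**The concern.** Two or more means a count of at least 2; more than two means a count of at least 3. Both statements are current text of the same protocol version, and they give opposite answers for a patient with exactly two factors.

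The cut-off matters because section 2 presents it as protection for people who may receive no active treatment. An enrolled patient stays on the allocated capsule for 12 weeks, and section 9.6 forbids any other lipid-affecting medication meanwhile. If section 2 states what was meant, sites that follow the criteria to the letter will randomize patients whom the sponsor meant to keep out. If criterion 1 states what was meant, section 2 describes a limit that the trial does not apply. Section 11.2 does not settle the matter: it acknowledges that "Patients enrolled in the study will have risk of lack of efficacy of study medication" and points to lifestyle advice, but says nothing about patients with two risk factors.

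**Working it through.** The check compares two texts and makes a small count. No sample size or power figure enters it.

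**Inputs**
- Section 2: not enrolled if the count is ≥ 2 (ATP III factors).
- Section 6.2, item 1: excluded if the count is > 2 (four listed factors).
- Section 6.1: ages 30 to 65, so the age factor is already present in men over 45 and women over 55.
- Sections 4.1.3 and 14.1: 98 patients, allocated 1:1.
- Section 4.1.4: 12 weeks of treatment.

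**Step 1: where the rules differ.** Apply both cut-offs to the four listed factors, each present or absent: 2^4 = 16 combinations.

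| Factors present | Combinations | Section 2 cut-off (≥ 2) | Criterion 1 (> 2) |
|---|---|---|---|
| 0 | 1 | may enter | may enter |
| 1 | 4 | may enter | may enter |
| 2 | 6 | barred | may enter |
| 3 | 4 | barred | barred |
| 4 | 1 | barred | barred |

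The section 2 cut-off bars 6 + 4 + 1 = 11 combinations and criterion 1 bars 4 + 1 = 5. The difference, 11 − 5 = 6, is the row with exactly two factors. These are counts of combinations, not shares of patients.

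**Step 2: does another criterion close the gap?** Take two patients who meet the lipid and other entry criteria.
- A 50-year-old male smoker with normal blood pressure and no family history has two listed factors (smoking, age). No other item in section 6.2 excludes him on that account.
- A 50-year-old non-smoking man on a stable antihypertensive dose, with controlled pressure and no family history, also has two (hypertension, age). Item 2 removes hypertension only above 160/100 mmHg or when the dose has changed within the last month, so he passes.

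Both may be randomized under section 6.2. By section 2's cut-off neither would be.

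**Step 3: does the reference to ATP III remove the conflict?** Section 2 refers to the guideline's factors and the protocol does not print them. The four in section 6.2 are the only list given. A longer guideline list would make section 2 stricter and leave all 6 disputed pairs in place. The conflict would shrink only if a printed factor were not a guideline factor, which nothing in the document suggests. Even if one were not, the other three would still form C(3,2) = 3 disputed pairs.

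**Step 4: exposure.** Planned placebo patients: 98 × 1/2 = 49. Duration: 12 × 7 = 84 days. If a share p of the 98 have exactly two listed factors, 98p are affected and 49p are expected on placebo. The protocol gives no basis for p, so the arithmetic range is the full one: 0 to 98 affected, 0 to 49 on placebo.

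**The case against.** The best counter-argument is that the criteria govern and sites will enrol consistently. Section 8.1 adds "There will be no protocol waiver in this study", so criterion 1 will be applied as printed. The fault may then be a loose phrase in a background paragraph. This stands in part: there is little ambiguity at the sites, and the document does not show that section 2 is the true intent. But consistent use of criterion 1 is exactly what admits patients whom section 2 says will stay out. The no-waiver sentence does not bear on which cut-off was meant.

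Other protections also count. Item 2 removes unstable or recent cardiovascular disease, and item 3 removes triglycerides above 500 mg/dL. Section 11.4 requires alternative treatments to be explained before consent. Section 6.3 lets the investigator withdraw a patient in the patient's interest. These limit the risk, but none addresses a patient with exactly two factors, and the withdrawal option operates only after enrolment.

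A reader might infer three stronger things that the documents do not support:
- **That ethics committees see only the stricter limit.** Section 11.3 has them review the whole protocol, including section 6.2, so they see two inconsistent statements.
- **That changing the number in criterion 1 would by itself deliver what section 2 promises.** Section 2 uses a guideline list that the protocol does not print, so a patient could still reach two guideline factors and pass the revised criterion.
- **That section 11.2 is a second contradiction.** Its silence on two-factor patients is an omission only.

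**Conclusion.** The contradiction is real. Section 2 and exclusion criterion 1 disagree for every patient with exactly two of the listed factors, which is 6 of the 16 combinations. Such patients are eligible for up to 12 weeks of placebo, contrary to a limit that section 2 justifies by the placebo design.

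The conclusion assumes that the four printed factors count as risk factors in section 2's sense. It does not assume which cut-off was intended, and it puts no number on the patients affected. It implies nothing about bias, power or the composition of the analysis sets. It is a clear inconsistency in an eligibility threshold tied to patient protection, and it should be corrected before the first patient is enrolled.

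**What to change.** Use one cut-off and one factor list in section 2, section 6.2 and the eligibility checks at Visits 1 and 2. There are two ways to do this, and the sponsor has to say which was meant.

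1. **If section 2 is right:** reword criterion 1 to exclude patients with 2 or more of the listed factors, and have section 2 refer to the list in 6.2 in place of an unprinted guideline list. The cost is a smaller recruitment pool, by an amount that the protocol gives no means to estimate.
2. **If criterion 1 is right:** correct section 2 to more than 2 of the factors in 6.2, and have the ethics committee confirm that 12 weeks of possible placebo is acceptable for patients with two factors. Recruitment is unaffected.

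Either way it is a short text change with ethics committee approval; option 1 also needs the eligibility item in the case record form to match. It is best made before enrolment opens, since section 8.1 says: "Amendments should be made only in exceptional cases once the study has started".
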